#### Concealment

At the initiation of treatment, all CETA providers, supervisors and trainers and participants are blind to whether a participant is randomized to Brief or Standard CETA. The informed consent describes the possibility of Brief vs. Standard to the participant. At the end of the fourth treatment session, the counselor reads a script to the participant reminding them that the next session may be the last session. Following completion of the fourth treatment session, the study staff team notifies the Johns Hopkins University (JHU) research team via email about the need to un-blind the Brief or Standard status. Only the study director and two analysts on the data monitoring team have access to the password-protected database linking study ID number to treatment status. Once an email request for un-blinding is received, the study director checks the randomized assignment and sends an email back to the research team, the supervisor, and the trainer with the participant status (Brief or Standard). The clinical supervisor then contacts the counselor to un-blind. This whole process is done within 24 hours of completion of the fourth treatment session so as to allow planning between counselor and supervisor for either ending or continuing treatment. The participant does not find out about Brief vs. Standard status until they arrive at the fifth session. If the participant is assigned to Brief but still interested in services, the counselor may give them a list of local services but may not continue seeing the client. The client is also prohibited from receiving CETA from another counselor while the trial is ongoing.

### Data analyses

#### Primary analyses

Study hypotheses will be tested using an “intent-to-treat” model. The primary and secondary outcomes of interest will be mental health symptoms and functioning measured monthly for 6 months for all groups. Given the longitudinal nature of the data, we will use mixed-effects regression models to estimate average treatment effects while accounting for shared variance of repeated measures within participant. Treatment effects will be measured based on within-person change in mean scores on the symptom and function measures. Statistical significance will be set at *p <* 0.05. We will use Cohen’s *d* effect sizes to express the magnitude of the difference between treatment groups. Missing data will be explored as to the mechanism of missingness. If appropriate to assume missing completely at random or missing at random, we will use multiple imputation with chained equations to impute all missing data, including outcomes for those lost to follow-up [55, 56].

##### Analysis for secondary aims

Analysis of the implementation data will include examination of distribution of scale-level scores represented as average responses for all items in each scale. Individual-level items with average scores lower than the average score on the scale will be considered possible barriers and used to identify program implementation areas that could be improved. Finally, we will examine whether more positive experiences of implementation, as measured by higher average scores on each implementation scale, is associated with different treatment conditions, client outcomes, and provider characteristics. For the free listing responses from consumers, a full list of these responses and the frequency with which they were reported will be compiled. The provider FGDs will be analyzed using methods described in the Design, Implementation, Monitoring and Evaluation (DIME) manual 1 [57]. Briefly, notes will be taken during discussions and then thematically coded using emergent coding. Notes and coding will be done in the local language and then summarized before translation.

#### Planned secondary analyses

We will examine changes in client symptom trajectories after delivery of each component of CETA (i.e., elevation, slope, and both elevation and slope), using the clinical monitoring form (symptom questions only in Table 2). To do this, we will use the modeling approach detailed by Singer and Willet [58] to examine changes in client symptom trajectories after delivery of each component of CETA (i.e., elevation, slope, and both elevation and slope). This approach involves adding time-varying dichotomous indicators representing whether each participant has completed each of CETA’s components. This will allow us to look at whether clients’ symptom levels significantly decreased (elevation) or whether they had significantly faster improvement (slope) immediately following completion of certain components. We will compare these changes in trajectories to monthly change in the control group participants.

We will further analyze the clinical monitoring from data (symptom questions only in Table 2) by using survival analysis to calculate the number of sessions that it takes for clients to achieve reliable change using the Reliable Change Index (RCI) [59]. Clients who end or drop out of treatment will be censored. We will use control group data to predict the number of sessions required to achieve improvement in the absence of intervention. We will then adjust for the difference between the average improvement slopes for each condition in the survival analysis.

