**Discussion:**

This trial is the first rigorous study comparing a standard-length (8–12 sessions) modular, flexible, transdiagnostic, cognitive-behavioral approach to a shortened version of the approach (five sessions). Brief CETA entails “front-loading” with elements that research suggests are strong mechanisms of change. The study design will allow us to draw conclusions about the effects of both Brief and Standard CETA as well as which elements are integral to their mechanisms of action, informing future implementation and fidelity efforts. The results from this trial will inform future dissemination, implementation and scale-up of CETA in Ukraine and contribute to our understanding of the effects of modular, flexible, transdiagnostic approaches in similar contexts.

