### Interventions

#### CETA intervention

As described in the introduction section, the Common Elements Treatment Approach (CETA) is a modular, flexible, transdiagnostic approach developed by our team specifically for use by providers who need not be formally trained mental health professionals. The number of elements was purposefully limited to help with training, mastery, and scalability. Elements are cognitive-behavioral and include: Engagement, Introduction, Thinking in a different way 1 and 2 (i.e., cognitive processing), Talking about difficult memories (i.e., imaginal exposure), Relaxation, Getting Active (i.e., Behavioral Activation), Problem solving, and a Cognitive-behavioral approach to substance abuse (see Table 3). The implementation of CETA elements can vary on: (1) selection of elements, (2) order of elements, and (3) dose of elements depending on symptom presentation. Providers are taught to use an assessment tool and what the client “does and says” to determine the primary problem(s). Elements are chosen based on the primary problem(s) with orders that mimic evidence-based treatments. For example, if someone comes in with primarily trauma-related problems such as nightmares, avoiding trauma-related stimuli, but also other problems (e.g., sadness, not engaging in pleasurable activities, relationship issues), an initial choice and order of elements would mimic trauma cognitive-behavioral treatments of: Engagement/Introduction, Thinking in a different way 1, Talking about difficult memories (usually two to five 1-hour sessions), and Thinking in a different way 2 (usually one to two 1-hour sessions). If depressive symptoms are still present after these elements are delivered, or if strong depressive symptoms are interfering, the element of Getting Active (i.e., Behavioral Activation) may be added. As developed, CETA can provide individualized targeting of treatment with the number of sessions delivered dependent on reduction in symptoms. Further details can be found in a description paper [21] and within the two clinical trials published to date on CETA [26, 28].

**Table 3 Tab3:** Elements of Common Elements Treatment Approach (CETA)

Element	Simplified name (used in training)	Description

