We developed a Brief CETA version with five sessions to address concerns around scalability and time limitations within low-resource settings and certain contexts. All Brief CETA flows include one cognitive element and one behavioral element, and an introduction session. (See Fig. 3). Counselors, supervisors and trainers first agree on a primary presenting problem (trauma, depression, anxiety, or substance use). Each problem area has a set flow of certain elements based on evidence-based treatments for these primary areas. For example, the two most commonly used evidence-based elements in treatments for trauma are Cognitive coping/restructuring and Gradual desensitization or exposure [50, 51]. For depression, most evidence-based treatments include Cognitive coping/Restructuring and/or Behavioral Activation, thus the Brief CETA flow contains only these. Since Cognitive coping/Restructuring is present in all flows, this may be used to target multiple or varying symptomatology (e.g., depression thoughts, unhelpful thoughts related to the traumatic event).

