**Fig. 3 Fig3:**
[figure not shown]
Example Common Elements Treatment Approach (CETA)-Brief flows

Since randomization occurs after the fourth session, all participants begin with one of the Brief CETA five-session flows. Those randomized to Standard CETA receive additional sessions based on the Standard CETA protocol including evaluating: (1) client report of symptoms, (2) what the client does and says, and (3) supervision. A provider needs to provide at least three additional sessions, and more could be provided as needed. Completion of Standard CETA is based on decreased symptoms, improvement report by client, and supervisor approval. This Standard CETA arm models a clinical “stepped care” approach wherein a client would be offered a “front-loaded Brief CETA” first, and then if symptoms persist, treatment can be augmented with additional sessions and/or elements [52].

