
### Outcome and study measures

The study’s primary aim is to determine intervention effectiveness comparing Standard to Brief CETA, and both to a control group. For this aim, the primary outcomes are symptoms of depression, PTS, and impaired functioning (Tables 1 and 2) measured on a monthly basis for 6 months. Secondary outcomes include symptoms of anxiety and problematic alcohol use, also measured on a monthly basis for 6 months (see Tables 1 and 2 and Fig. 1). Outcome assessments for our primary aim of determining intervention effectiveness are done at baseline prior to randomization, and on a monthly basis for approximately 6 months.

All data is collected via self-administered digital survey on an electronic tablet device using CommCare [33]. Baseline assessments are done at a central location or at another private location convenient to the participants. Monthly assessments consist of the same symptom and functioning items as the baseline assessment (Table 2). For the control group, the study staff sets up monthly assessment appointments to be done at a central location and are self-administered on CommCare with the same symptom and functioning items as the baseline assessment (Table 2).

For the treatment groups, the monthly assessment is incorporated into a clinical monitoring form (Table 2). The clinical monitoring form includes the impaired function items every fourth visit (i.e., monthly) rather than on a weekly basis. The clinical monitoring form is self-administered on CommCare at the beginning of each CETA session and helps guide the course of treatment. After treatment ends, participants continue to be monitored monthly with the same assessment (Table 2) via in-person visit (or phone call if in-person is not possible) by the study team. At the last assessment (6 months post treatment), some additional demographic- and alcohol-related questions are administered to measure potential pre-post change on these characteristics.

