### Randomization, concealment, un-blinding

All eligible and consented adults are randomly allocated by a computer-generated randomization algorithm to either a wait-list control condition, the Brief CETA model, or the Standard CETA model. The unit of randomization is the individual. Block randomization is used to ensure equal distribution of treatment and control participants across providers. Within a provider, we randomly allocate 20 participants using a 1:2:2 (control:Brief:Standard) allocation ratio. Participants, counselors, study staff, and all clinical supervisors are blinded to study group allocation between Brief and Standard CETA conditions. This is done in an effort to ensure that all participants across both Brief and Standard CETA conditions will receive comparable treatment (see section “Concealment” below).

Study group allocation, either treatment or control only, is revealed to eligible participants immediately following the baseline assessment. If assigned to begin treatment right away, the study staff assigns a participant to a counselor based on availability and location of treatment. Counselors set up an initial meeting with the participant within 10 days of the baseline assessment. If assigned to control, the study staff set up a study assessment visit approximately 30 days after the completed baseline assessment.

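### The component analysis can yield exploratory associations, but not the conclusions about active elements that the abstract and discussion announce

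*Protocol article*

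**What the plan says.** The Planned secondary analyses section takes client symptom trajectories from the clinical monitoring form and models a change in elevation, slope or both after each element: "This approach involves adding time-varying dichotomous indicators representing whether each participant has completed each of CETA’s components". The comparator is the wait-list: "We will compare these changes in trajectories to monthly change in the control group participants".

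Other sections fix how elements reach clients:

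- Randomization, concealment, un-blinding: "The unit of randomization is the individual". Allocation is to control, Brief or Standard (1:2:2). No element is allocated at random.
- CETA intervention: "Each problem area has a set flow of certain elements based on evidence-based treatments for these primary areas", and "all participants begin with one of the Brief CETA five-session flows". The cognitive element is in every flow.
- CETA intervention, on elements after the initial choice: "If depressive symptoms are still present after these elements are delivered, or if strong depressive symptoms are interfering, the element of Getting Active" may be added. Standard clients get at least three further sessions. More are given as needed, and treatment ends on symptom reduction, client report and supervisor approval.
- Outcome and study measures: "The clinical monitoring form is self-administered on CommCare at the beginning of each CETA session and helps guide the course of treatment".

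The conclusion announced in the abstract's Discussion paragraph is that the design will permit inferences about both versions "as well as which elements are integral to their mechanisms of action, informing future implementation and fidelity efforts". The main Discussion repeats it. The abstract's methods paragraph and Study aims describe the same work as exploration or examination.

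**The concern.** A completion indicator estimates an element's effect only if, given everything else in the model, whether and when the element was completed is unrelated to how the client would have progressed anyway. Two stated features of delivery work against this.

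First, within a flow in sessions 1-5, completion of an element is close to a function of session number, so the indicator competes with the time trend for the same information. Every treated client is planned to receive the cognitive element, so no treated group without it exists for comparison.

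Second, after session 5 the choice of element, and the number of sessions beyond the three required ones, depend on symptoms. The form that supplies the outcome also steers treatment, which is confounding by indication.

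The wait-list shows monthly change without CETA. It can help judge a package, but it cannot tell one element from another, or from time spent in treatment.

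At stake is the use the authors intend: guiding future implementation and fidelity work. An element could be kept or dropped because of where it sits in a flow or who was given it.

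**Working it through.** **Figures in the plan.** There is none to reproduce for this analysis. The Sample size section covers the arm comparisons only (89 in each CETA group), and non-random assignment is not cured by adding clients.

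**Check 1: false steps from the time trend.** Assume no element has any effect and the score at form s is y(s) = 4 + 8 × 0.5^((s−1)/h), so form 1 scores 12. Half-times are h = 3, 4 and 6 sessions. Fit an intercept, a time trend and step indicators switching on at form 3 and, for longer courses, form 6. The curve, the steps and the linear trend are all assumptions; the article states no form for time.

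Worked case, 5 forms, h = 3, linear time (t = s−1):

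- Scores: 12, 10.35, 9.04, 8.00, 7.17.
- Pooled within-segment slope = [0.5 × (10.35 − 12) + (7.17 − 9.04)] / (0.5 + 2) = −2.69 / 2.5 = −1.08.
- Segment means 11.17 and 8.07, difference −3.10. Mean times 0.5 and 3, difference 2.5.
- Step = −3.10 − 2.5 × (−1.08) ≈ −0.41 (unrounded inputs), where the truth is 0.

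All cases (range over h):

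| Forms | Form 3 step, linear | Form 6 step, linear | Form 3 step, quadratic | Form 6 step, quadratic |
|---|---|---|---|---|
| 5 | −0.14 to −0.41 | none | +0.01 to +0.06 | none |
| 8 | −0.40 to −1.09 | +0.12 to +0.38 | −0.01 to −0.03 | +0.02 to +0.12 |
| 12 | −0.88 to −2.17 | −0.43 to −0.81 | −0.08 to −0.35 | +0.06 to +0.29 |

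A straight line fitted to decelerating improvement pushes the misfit into the indicators. One quadratic term removes most of it.

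**Check 2: trend shape and selection together.** Null simulation with 178 clients, 60 replicates per scenario, a mixed model with random intercept and slope, and linear time. Flows, variances and the rule for adding elements are assumed, because Fig. 3 is not shown. Share of replicates with p < 0.05 (nominal 5%):

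| True decline | Extra element given | Cognitive | Exposure | Behavioural | Extra |
|---|---|---|---|---|---|
| Straight | at random | 5% | 5% | 5% | 7% |
| Straight | if symptoms persist | 8% | 8% | 7% | 13% |
| Decelerating | at random | 10% | 67% | 53% | 68% |
| Decelerating | if symptoms persist | 87% | 20% | 27% | 42% |

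Monte Carlo error is about 3 to 6 percentage points. In the last row the cognitive element shows a mean false benefit of 0.68 points, and the other three show false harm of 0.36 to 0.54. In row 2, selection alone gives the extra element a mean of +0.16 points, a small bias under these assumptions. The cognitive indicator correlated 0.73 with session number.

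**Check 3: what can be identified.** Four presenting problems and five sessions give 20 flow-by-session cells. Under set flows each indicator is constant within a cell, so session effects fitted separately by flow have rank 20 with or without the indicators: nothing is left to estimate. A session effect common to all flows plus a flow main effect has rank 4 + 5 − 1 = 8. Indicators then remain estimable wherever flows place elements at different sessions.

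**Check 4: readings after session 5.** Forms precede sessions, so the form before session 6 follows session 5. Standard clients have that form. Brief clients do not; their next reading is a monthly post-treatment assessment, which Planned secondary analyses does not name for client trajectories.

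**The case against.** The strongest defence is that the analysis is labelled exploratory in the abstract's methods paragraph and in Study aims, touches neither primary hypothesis, and uses a recognised modelling approach. An article may leave the shape of the time trend to an analysis plan. This stands as far as it goes: running the analysis is no error, and the absence of a stated trend is no finding. It does not rescue the announced conclusion, which credits the design with more than the aims claim.

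A reader might go further than the documents allow in several ways:

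- *That the sample is too small, or that nothing can be estimated.* The obstacle is how elements are assigned. Associations are estimable where flows differ and where Standard providers vary elements after session 5. With a straight decline and random extras, false-positive rates were 5-7%.
- *That the model is linear, so the larger false steps apply.* The article does not say so, and a curved trend removes most of them.
- *That start-of-session forms are a defect.* The next form follows the completed element. The only gap is after the last session.
- *That an element finished in session 5 is never seen.* Standard clients have a later form, and monthly readings with the same items exist. With Fig. 3 not shown, it is also unknown whether any element first completes in session 5.
- *That all later elements go to poor responders.* Three extra Standard sessions are required whatever the symptoms. Only element choice and sessions beyond those can follow symptoms.
- *That early elements are always favoured.* The direction changed with the scenario.

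**Conclusion.** The point holds as a mismatch between an observational component analysis and a conclusion presented as following from the design. That elements are unrandomised, follow set flows and are later chosen partly on symptoms is stated in the article and needs no assumption. The randomised contrasts support causal statements about Brief versus Standard, and each versus wait-list, as packages only.

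The size of the bias is conditional. Under the assumed curves, false steps reach 2.2 points with a linear trend over 12 sessions. With a quadratic term they stay below 0.13 over 5 to 8 sessions and at or below 0.35 over 12. Selection by symptoms remains whatever trend is fitted; its effect was small in the one linear-decline scenario that isolates it, and its size in the trial cannot be derived from the article. The matter deserves correction because it changes what the trial may conclude about elements. The primary results are unaffected.

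**What to change.** In Planned secondary analyses:

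- (a) Fit a non-linear session-number effect common to all flows, plus a flow main effect. Do not fit session effects within each flow, which would absorb the indicators.
- (b) For elements added after session 5, adjust for the score on the preceding form. This handles selection on the recorded score, but not on what the client says and does or on supervisory judgement.
- (c) Include the post-treatment monthly assessments, so that an element completed in session 5 has a later reading in Brief as well. The time term must allow for their wider spacing.

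In the abstract's Discussion paragraph and the main Discussion:

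- (d) Restate element results as exploratory, hypothesis-generating associations, consistent with the abstract's methods paragraph and Study aims, and limit causal conclusions to the randomised package comparisons. This is needed whichever model is chosen.

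The cost is some rewording and modest extra modelling on data already being collected. The price is wider intervals for element effects and a softer claim.
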